#### V. Experimental Design and Methods:

- i) Provide concise description of experimental design and procedures to be used to accomplish study goals. Include precise descriptions of all tests and measurements, and their expected duration. Include optional testing and blinding/un-blinding procedures if applicable.

#### Overview of Naltrexone Trial

The purpose of the study is to evaluate whether AGATE effectively measures and enhances medication adherence in the context of a naltrexone trial involving heavy drinkers. Participants will be heavy drinkers recruited from the greater Albuquerque area who are interested in either reducing or stopping their drinking and deemed to be candidates for naltrexone pharmacotherapy by the study physician, [name]. Those enrolled in the study will be prescribed naltrexone (at FDA-approved dose of 50mg once daily) for eight weeks. All participants will receive smartphones during the study. Participants will be randomly assigned to receive either AGATE (adherence support) or SASED, a web-based alcohol and side-effects diary via smartphone. The primary outcome will be percent of scheduled doses that were taken during the eight week trial, as measured by the Medication Event Monitoring System (MEMS, Aardex Group, Union City, CA), pill counts, and the timeline follow-back (TLFB) method. The secondary outcomes will be selected indicators of alcohol use over the 8-week trial.

**Procedures.** Potential participants will be screened by phone to determine basic eligibility criteria (i.e., criteria related to drinking/drug use, pregnancy and medications, etc., as outlined below). In most cases, participants will be responding to flyers, etc. and will call the research office. As noted above, we will also initiate contact with some former participants who had agreed to future contact. Those meeting basic eligibility criteria on the phone screening will be scheduled for an in-person screening visit. At the in-person screening visit participants will first meet with the study coordinator to review the details of the study. Participants will be assigned a randomly generated Unique Research Subject Identifier (URSI) number, following standard protocol at MRN. To obtain an URSI, research staff first enter basic demographic variables including name, address, and contact information into an operational database (the URSI database). Each subject is then provided with a random unique number (URSI) to maximally protect the confidentiality of their data across all modalities and forms of data collection. In most cases, each subject is only assigned a single URSI number even if they participate in multiple studies. This URSI also serves as an operational link to the subject's identity. Therefore, it is important to note that the URSI database is for operational purposes only and can never be used for research purposes. To this end, only the PI (and their designated staff) who enrolled the subject into the research study will have access to any of the demographic information associated with the URSI while the study remains open at with the HRRC. Specifically, the database will not allow other research staff to access this basic demographic information associated with an URSI number to maintain subject confidentiality (i.e., it is password protected).

Participants will next provide informed consent (see attached consent form). They will then provide a urine sample in a private bathroom at for purposes of a toxicology screen. Additionally, female participants will complete a urine-based pregnancy screen (in the event of a positive result, the participant will not be allowed to continue with the study). Participants will next report to the UNM Psychiatry Department Pharmacy (in the building adjoined to MRN) for blood work. A licensed phlebotomist will acquire a small blood sample (approximately 12-15ml) to test for complete blood count (CBC) and a liver enzyme panel, including examining levels of gamma-glutamyl transferase (GGT), to ensure that participants are appropriate candidates for naltrexone

treatment. Blood samples will be labeled by URSI number and sent to TriCore laboratories. A TriCore representative will pick up the samples on the collection day.

When participants' blood/urine samples have been analyzed (estimated 2-3 days after the screening visit), results will be placed in the participant's research study folder at MRN for review by [name], along with results of the pregnancy screen. If the patient is deemed a candidate for naltrexone based on blood/urine screens (see exclusion criteria), they will be scheduled for their baseline (Week 0) appointment. At that time, participants will be asked to remain abstinent from alcohol for 72 hours prior to their appointment to permit an assessment of potential withdrawal. If the patient is not medically eligible for naltrexone based on blood/urine screens, the [name] will call the participant to discuss the results, inform the participant of ineligibility, and provide a referral if indicated.

At the baseline (Week 0) visit participants will meet with the research assistant and [name] to further determine whether naltrexone is medically appropriate. Inclusion/exclusion criteria related to psychiatric diagnoses/medication and substance use factors will initially be evaluated by a project assistant trained in conducting clinical interviews ([name]). This interview will also include a CIWA (Clinical Institute Withdrawal Assessment) to assess potential withdrawal symptoms and a breathalyzer test to ensure a breath alcohol content of 0. A score of 8 or higher will be an exclusion criterion; if such an event occurs the participant will be immediately referred to the UNM Hospital emergency department and excused from further participation. If the participant appears to meet any other exclusion criteria, [name] will consult with [name] to verify that the participant should be excluded; [name] will then follow up with the participant to discuss referral options.

If the participant fulfills study criteria based on this interview, the participant will proceed to meet with [name] for a medical assessment immediately afterward. Assessments will be conducted in a CPR clinic room and will consist of a physical examination and brief medical history interview. The medical screen will also include assessment of whether the participant has a current primary care provider (PCP) to ensure that participants will have access to a physician to continue naltrexone following study completion, if indicated. If a participant does not have a PCP [name] will refer the participant to the UNM primary care clinic and recommend they establish a PCP as soon as possible. For female participants, medical visits will include discussion of birth control during the study and participants will be required to complete a menstrual log, which will be reviewed by [name] in subsequent medical visits.

If any medical or psychiatric contraindications are noted at the baseline visit (summarized under exclusion criteria) the participant will be informed that they do not meet full eligibility criteria, given a referral as appropriate, for the visit at \$20/hour, and excused from further participation. If participants are considered good candidates for naltrexone based on the medical screening, [name] will place an order with the UNM Psychiatry Department pharmacy for the prescription. Participants receiving naltrexone will also be provided with a wallet card to carry with them which, in case of any medical emergency, is intended to notify physicians, or emergency medical teams that the participant is taking naltrexone. This is important for the participant's safety given that naltrexone is an opioid antagonist, thus, administering opiate-based pain medications may be ineffective or dangerous and should be avoided (or implemented only with caution).

Next, the participant will continue the baseline appointment by completing a set of study questionnaires (see Table 1 below and Appendix II, Study Measures). Questionnaires will be administered by computer and will take approximately 1-2 hours to complete. Participants will be seated alone in one of the five private clinical assessment rooms at MRN. Computerized questionnaires will be delivered using a secure, web-based interface programmed by Talaria, which has been used in previous studies (see Appendix III for security information). Therefore, responses (identified only by URSI number) will be stored on a secure server maintained by Talaria Inc., and will not be accessible on local servers or computers after the participant has completed the measures.

Following completion of questionnaires the participant will meet with the study coordinator for detailed instruction on using the study cell phone and responding to prompts delivered by the cell phone. The participant's URSI number (which will have been randomly generated using the procedures outlined above) will be entered into the AGATE/SASED administrative interface, where computerized randomization will occur. This system is maintained by Talaria, but accessible via a web interface by the study research assistant using a secure password. At this time the participant will be asked to select a drinking goal: abstinence or moderation (moderation will be defined by the participant). Once the URSI number is entered, the computer randomization algorithm will block participants according to gender and drinking goal (abstinence or moderation), ensuring even distribution of these variables between conditions. The study coordinator will provide the participant with a study smartphone (Blackberry 8330 or equivalent) and instruct the participant in its use. This will include basic functions of the phone, how to respond to SMS prompts, and guidelines for acceptable use of the phone during the study (described below). Participants will also provide a saliva sample for analysis of a genetic variant in the mu opioid receptor gene (OPRM1 A118G, rs1799971), which is demonstrated to influence response to naltrexone (Anton et al., 2008; Ray & [name], 2007). Saliva will be collected in a plastic tube, labeled with the URSI number, and stored in a secure freezer in the neurogenetics lab at MRN. Samples will remain there until they are destroyed (10 years following study completion). Genetic analyses will be conducted in the neurogenetics lab at MRN. OPRM1 will be evaluated as a predictor of response to naltrexone in secondary analyses.

Finally, the participant will pick up his/her 4-week prescription for naltrexone at the UNM Psychiatry Department pharmacy. The pill container will be fitted with a MEMS monitoring system by the pharmacist, which will track the date/time of each time the container is opened. This data, which is stored in a microchip in the MEMS cap. The pillcap will not be linked to any personal identifier or URSI. The data will be downloaded when the participant returns for subsequent visits and labeled by URSI at that point. Data (timestamps) on pillcap openings will be linked to URSI in a password-protected spreadsheet kept on a password-protected computer at MRN. At the end of the baseline appointment participants will be encouraged to contact the study coordinator with any questions, concerns, or problems related to study participation. They will also be encouraged to contact [name] directly with any questions about the study medication or side effects.

Following the baseline visit, the course of the medication trial will be 8 weeks. During this time participants will come back to MRN/UNM CPR for follow-up medical visits (at weeks 4 and 8). This timeframe is consistent with recommended clinical guidelines for monitoring patients on naltrexone (Anton, 2008). At the Week 4 visit, participants will first be interviewed by the research assistant, who will assess potential side effects using a standard side effects checklist. Results of the interview (i.e., any side effects reported) will be placed in the research folder for [name] to review. Participants will also bring medication bottles for pill counts and uploading of MEMS pillcap data. They will report whether they have had any problems with their study phone or AGATE system.. Participants will report whether they have had any problems with their study phone. Any problems will be documented and addressed. Participants will also complete a brief subset of the study questionnaires again (e.g., assessing drinking and medication adherence in the last 4 weeks, see Table 1). Similar to the baseline visit, participants will be seated alone in a private assessment room at MRN and will complete measures using the web-based interface. Next, a follow-up blood sample will be obtained in the Psychiatry pharmacy using the same procedures and tests as described in the screening visit. Then the participant will meet with [name] for a follow-up medical assessment. [name] will review the contents of the participant's research study folder (e.g., side effect checklist) and interview the participant. If any medical contraindications to continuing naltrexone are evidenced, naltrexone treatment will be discontinued immediately. In these cases, [name] will discuss with the participant an appropriate referral plan. To avoid threats to internal validity, [name] will be blind to study condition (AGATE/SASED). For this reason, she will not discuss aspects of AGATE or barriers to adherence with participants; the interview will be focused on side effects and medical/safety issues. If no contraindications to continuing naltrexone are evidenced, participants will be provided with the next 4-week naltrexone prescription, which will be sent to the pharmacy. Again, pill vials will

be re-fitted with a MEMS monitoring system pillcap. Participants will not be allowed to take home their prescription on this day, pending results of the blood screen. When the results of the Week 4 blood screen are available, they will be placed in the study chart for review by [name]. If no problems with the bloodwork are evidenced, the research assistant will contact the participant and ask that they pick up their prescription from the pharmacy. If any concerns are noted that suggest medication should be discontinued, [name] will call the participant to inform them.

At week 8 the study physician will complete a visit identical to week 4 (i.e., it will include the same questionnaires, pill counts, blood draw, and medical visit). However, participants will be discharged at the end of the week 8 visit. At the medical assessment, [name] will provide a discharge recommendation. Participants who show evidence of a good clinical outcome to naltrexone will be referred to their PCP. At the end of the 8 week visit the study coordinator will also conduct an exit interview to elicit qualitative information on the usability and acceptability of AGATE/SASED.

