#### VI. Human Subjects:

- i) Describe characteristics (inclusion criteria) of subject population, including precautions to be taken with vulnerable populations (e.g. children, prisoners, mentally ill/disabled person). Answer for each subject group, if different.

**Participants and Recruitment.** Participants will be heavy drinkers, (ages 21-55) with average weekly consumption  $\geq 14$  standard drinks for women and  $\geq 21$  standard drinks for men over the past 3 months (see below for full inclusion/exclusion criteria). Participants will be recruited primarily using posters/fliers, radio announcements, and newspaper advertisements, using procedures identical to a recently completed pharmacotherapy study for alcohol dependence conducted by [name], who is a co-Investigator in this proposal (HRRC# 07-228). In addition, we may recruit participants who have participated in other studies in the [name] lab, provided that they a) gave consent to be contacted about future studies, b) indicated at the time of participation that they were seeking treatment for alcohol problems or wanted to reduce their drinking (most of [name] studies assess whether the participant is treatment-seeking), and c) meet all other eligibility criteria. Such participants will be identified using existing records and contacted by phone to assess interest in the study. We will not attempt to recruit participants who have taken medication as part of another study in [name] lab. Participants who were screened for a recent study on olanzapine for alcohol dependence (HRRC# 07-228) and did not qualify based on reasons specific to olanzapine may be contacted and assessed for eligibility for treatment with naltrexone in this study.

Eligible participants must meet the following inclusion criteria:

1. Age 21-55
2. Report an average weekly consumption of  $\geq 14$  standard drinks for women and  $\geq 21$  standard drinks for men over the past 3 months (Anton et al., 2006).
3. Report at least two heavy drinking days (defined as 4+ drinks for women and 5+ drinks for men) in a consecutive 30-day period within the 90 days prior to baseline evaluation (Anton et al., 2006).
4. Participants must endorse a desire to reduce or stop drinking alcohol and willingness to try naltrexone.

5. Participants must receive medical clearance by the study physician to take naltrexone (based on blood panels and a medical evaluation).

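### The protocol asks heavy drinkers to stop alcohol for 72 hours before any stated step asks about past alcohol withdrawal, seizures or delirium

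*Protocol*

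**What the plan says.** Protocol section V i), under Procedures, sets this order.

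- **Phone screen.** It covers basic eligibility: "criteria related to drinking/drug use, pregnancy and medications, etc., as outlined below".
- **Screening visit.** Study overview, consent, urine toxicology, a pregnancy test for women, and blood for a blood count and liver panel. Section VI v) describes the visit the same way.
- **Booking of Week 0.** "If the patient is deemed a candidate for naltrexone based on blood/urine screens", the appointment is made, and at that point "participants will be asked to remain abstinent from alcohol for 72 hours prior to their appointment to permit an assessment of potential withdrawal".
- **Week 0.** "Inclusion/exclusion criteria related to psychiatric diagnoses/medication and substance use factors will initially be evaluated by a project assistant". The same interview includes the CIWA and a breathalyzer test. A CIWA score of 8 or higher excludes the person and leads to immediate emergency referral. The physician's assessment follows: "a physical examination and brief medical history interview".
- **Questionnaires.** These come after the medical assessment: "Next, the participant will continue the baseline appointment by completing a set of study questionnaires".

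On the population, section VI i) says: "Participants will be heavy drinkers, (ages 21-55) with average weekly consumption" of at least 14 standard drinks for women and 21 for men. It gives no upper limit, and a note says that alcohol dependence is not required. The only entry criterion on withdrawal is exclusion 8, the CIWA at baseline.

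**The concern.** The protocol treats withdrawal as a hazard: it asks for abstinence in order to look for it, and it sends anyone scoring 8 or more on the CIWA to emergency care. The abstinence itself takes place at home, at the study's request. The only stated gate before it is laboratory candidacy for naltrexone, and whether someone can take naltrexone is a different question from whether that person can safely stop drinking abruptly without supervision.

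Some participants would not otherwise stop. Inclusion item 4 accepts a wish to reduce drinking, and moderation is one of the two drinking goals offered at Week 0. A person with severe withdrawal in the past could therefore pass every stated step and begin the 72 hours without having been asked about it. What is at stake is participant safety, not the analysis.

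**Working it through.** The protocol states no figure on this point, so the check is mainly one of sequence. Counts are given for scale.

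**1. What is stated before the request, and what after.**

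| Step | When | Stated to ask about past withdrawal? |
|---|---|---|
| Phone screen | Before | Not named; the list is open-ended |
| Consent, urine and blood tests | Before | No |
| Review of results for naltrexone candidacy | Before | No |
| Request for 72 hours without alcohol | – | – |
| Clinical interview with CIWA | After (Week 0) | Not named; the CIWA is for withdrawal symptoms |
| Physical examination, brief medical history | After (Week 0) | Not named |
| Questionnaires (Table 1, Appendix II) | After (Week 0, last) | Contents not shown; too late in any case |

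**2. Entry criteria.** The phone screen refers to the criteria listed later, so those were read in full.
- Inclusion: 6 legible items (item 7 is blank in this copy). Items on past withdrawal: 0.
- Exclusion: 11 items. Items on past withdrawal: 0.
- Total: 0 of 6 + 11 = 17. Items on current withdrawal: 1 of 17 (exclusion 8, assessed at baseline).

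**3. Intake.** The entry minimum is 14 / 7 = 2 drinks a day for women and 21 / 7 = 3 for men. At that floor intake is modest; the concern lies with the uncapped upper end and with people who have had withdrawal before.

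**4. Number of people asked.** Section VI ii) plans about 140 people at in-person screening and a 25% loss for medical reasons: 140 × (1 − 0.25) = 105, which matches the randomisation target.
- If all 35 losses (140 − 105) came from blood or urine results, 105 would be asked to abstain.
- If none did, 140 would be asked.

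**5. Cost of asking first.** The share referred because of their history is not in the document. Assume 1% to 5% of those otherwise cleared.
- At 1%: 105 / (0.75 × 0.99) = 141.4, so 142 in-person screenings.
- At 5%: 105 / (0.75 × 0.95) = 147.4, so 148.

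That is 2 to 8 more than 140. For a given referral share this is an upper limit, because some of those referred would have failed at Week 0 anyway.

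**The case against.** The strongest reply is that this argues from silence. The phone screen covers drinking and its list is left open, so a question on past withdrawal may be in the script. The consent form, signed before the request, may carry a warning. Neither is in this copy. That stands as a limit: a reader might infer that the trial never asks about past withdrawal, and the document does not support that. It supports only that no stated criterion or step before the request asks.

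A reader might also infer that nothing but intake and laboratory values is known when the request is made. That is too strong. The phone screen also covers drug use, pregnancy and medications, and toxicology, blood count and liver results are reviewed first. None of these is stated to address past withdrawal.

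The protocol has other safeguards. Participants want to cut down or stop, they are asked and not compelled, and the 72 hours serve a safety assessment with emergency referral behind it. All true, but the referral works only for someone who reaches the visit. The physician's clearance under inclusion item 5 is for taking naltrexone, and the medical evaluation it rests on takes place at Week 0.

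Finally, the Week 0 test is "a breathalyzer test to ensure a breath alcohol content of 0", and one might fault it for not confirming 72 hours. The protocol never says that it does, and it comes after the period in question, so no point is made of it.

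**Conclusion.** The concern holds as a matter of sequence. Followed exactly as written, the protocol has heavy drinkers of any intake above the minimum stop alcohol for 72 hours before any stated question on past withdrawal, seizures or delirium, and before interview, CIWA, history or examination. This goes beyond missing detail because the order is fixed in the text and the abstinence is requested by the study.

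Its size is limited. Between 105 and 140 people would be asked, only some would be at any risk, and the rate of withdrawal cannot be estimated from the document. A reader might take the range as a count of people in danger; it is not one. The conclusion assumes that the unseen phone script and consent form do not already deal with the matter. That a history of withdrawal, seizures or delirium is the right thing to ask about is a clinical judgement, not something the protocol states. This is a cheap improvement worth making for participant safety, with no bearing on the analysis.

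**What to change.** At the existing screening visit, ask about past alcohol withdrawal, including seizures and delirium. Put the answer, with the intake already reported by phone, in the research folder that is reviewed with the laboratory results. State that the study physician then clears the 72-hour instruction for each participant, or refers those at high risk instead of asking them to abstain. If the phone script already asks these questions, it is enough to say so in the protocol and add the physician's clearance.

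The cost is a few questions at an existing visit and some protocol wording, with no new visit. Some people would be referred instead of enrolled: under the assumed 1% to 5%, in-person screenings would rise from 140 to between 142 and 148 at most. The target of 105 randomised and the analysis stay as they are.

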### III. Hypothesis or Study Goals (questions hoped to be answered by study):

The overall goal of the study is to evaluate the efficacy of a new smartphone-based technology for tracking and enhancing medication adherence. The technology, AGATE (Adaptive Goal-Directed Adherence Tracking and Enhancement), was recently developed by our colleagues at Talaria, Inc. (Seattle, WA) for the purpose of enhancing medication adherence for individuals with alcohol problems. In the current study we will test the efficacy of AGATE for increasing medication adherence in an eight-week pharmacotherapy study of naltrexone. Participants will be randomly assigned to smartphone-based adherence support (AGATE) or a control condition (smartphone alcohol and side effects diary, SASED). A secondary goal is to examine medication effects on patterns of daily drinking using ecological assessments permitted by cell-phone assessments.

The specific hypotheses are as follows:

**Hypothesis 1:** Those assigned to the AGATE condition will be more likely to be classified as adherent to naltrexone (e.g., taking 80% or more of scheduled doses) over the course of the study compared to those assigned to SASED.

**Hypothesis 2:** Those in the AGATE condition will take significantly more scheduled doses compared to those in SASED.

**Hypothesis 3:** Those in the AGATE condition will show better drinking outcomes (defined as higher percentage of days abstinent, lower percentage of heavy drinking days, fewer drinks per drinking day, and longer latency to first heavy drinking day) compared to SASED.

**Hypothesis 4:** Those in the AGATE condition will report higher satisfaction with treatment compared to SASED.

**Hypothesis 5:** Medication adherence will moderate the effect of naltrexone on drinking outcomes, such that the effects of naltrexone on reduced heavy drinking will be increased among those with higher rates of adherence.

**Hypothesis 6:** Adherence outcomes will mediate the effects of condition assignment (AGATE vs. SASED) on drinking outcomes.

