### **Data Access/Sharing.**

As described above, all data collected via cell phone and web-based questionnaires will be stored by Talaria on secure servers. Clinical data collected at MRN/UNM will be stored at MRN in the lab of [name]. All clinical data will be kept in research folders in a locked file cabinet, identified only by URSI number. For the purposes of data analyses at the end of the study, [name] will send a password-protected electronic data file to [name], containing coded clinical data (e.g., diagnostic data, side effects, etc.) which will be labeled only by URSI number. Data from the two sites will be merged by [name] and sent back to [name] so both investigators can assist with data analyses.

Additionally, consistent with other studies in [name] lab, we will seek participants' permission for data sharing in the event they participate in more than one study in our lab or at MRN. MRN has a standardized data sharing procedure based on URSI number). Participants will respond to a separate box on the consent form to indicate whether they agree to data sharing.

---

iii) Describe methods by which data will be analyzed and interpreted. Include the following, if applicable:

Data will be analyzed using traditional General Linear Model analyses, e.g., a mixed-groups ANOVA to evaluate main effects intervention condition (AGATE vs. SASSED) pm adherence over the course of the study.

---

iv) Specific description of any experimental drug, device, or procedure. Any substance or instrument to be used in or on humans which has not received FDA approval for the proposed use requires an IND, IDE, or approval of the Radioactive Drug Research Committee.

N/A

- v) Specific description of any use of biological samples. This is to include their origin, links to identifying information, storage, access, and future use.

Participants will provide a saliva sample for analysis of a genetic variant in the mu opioid receptor gene (OPRM1 A118G, rs1799971), which is demonstrated to influence response to naltrexone (Anton et al., 2008; Ray & [name], 2007). Saliva will be collected in a plastic tube, labeled with the URSI number, and stored in a secure freezer in the neurogenetics lab at MRN. Samples will remain there until they are destroyed (10 years following study completion). Genetic analyses will be conducted in the neurogenetics lab at MRN. OPRM1 will be evaluated as a predictor of response to naltrexone in secondary analyses.

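### Allocation is blocked on gender and drinking goal, but the one analysis model the protocol names as an example does not carry them; naming them is a nearly free gain in precision

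*Protocol*

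**What the plan says.** Protocol, section V, item i (Procedures, randomisation paragraph): "the computer randomization algorithm will block participants according to gender and drinking goal (abstinence or moderation), ensuring even distribution of these variables between conditions". Two binary factors give four strata. Block size and allocation ratio are not stated.

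Protocol, section V, item iii, the only statement on analysis, opens: "Data will be analyzed using traditional General Linear Model analyses, e.g". The example that follows is "a mixed-groups ANOVA to evaluate main effects intervention condition (AGATE vs. SASSED) pm adherence over the course of the study". No blocking factor or baseline covariate is named, and none is excluded.

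On outcomes, the overview of the trial says: "The primary outcome will be percent of scheduled doses that were taken during the eight week trial". Hypothesis 3 adds drinking outcomes, among them "higher percentage of days abstinent, lower percentage of heavy drinking days, fewer drinks per drinking day", and also latency to the first heavy drinking day. Item iii names no model for these.

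On baseline drinking, the inclusion criteria in section VI require weekly consumption, with separate thresholds for women and for men, the latter counted in "standard drinks for men over the past 3 months", and a minimum number of heavy drinking days before baseline. Drinking history therefore has to be obtained before randomisation.

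**The concern.** When allocation is balanced within strata, differences between strata no longer contribute to the chance variation of the treatment difference. An ANOVA that leaves the strata out still counts those differences in its error term. The reported standard error then describes simple randomisation, which this trial does not use, and it exceeds the true one to the extent that the strata predict the outcome.

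Precision is at stake. Confidence intervals would be wider than the design justifies, and the test would run below its nominal level. There are reasons to think the factors matter, most clearly for drinking. A participant who chooses abstinence as the goal is aiming at the top of the percent-days-abstinent scale, and the protocol itself sets different drinking thresholds for women and men. For adherence the case is weaker. The Background cites a graded association between drinking and non-adherence, but reports nothing on gender or goal as predictors of doses taken.

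Baseline drinking is a separate matter. It is not an allocation factor, so leaving it out does not make the reported standard error wrong for the design. It only forgoes precision, chiefly for the Hypothesis 3 outcomes.

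**Working it through.** **The plan's own figures.** Section VI, item ii gives 105 randomised and 88 at endpoint. The recruitment arithmetic agrees: 140 × (1 − 0.25) = 105, and 88/105 = 83.8% retained. No significance level, power or effect size accompanies these numbers, so there is no power calculation to reproduce.

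**Inputs for the check**
- 88 at endpoint (protocol); 44 per arm (assumed equal allocation).
- Two-sided 5% level and 80% nominal power (assumed).
- SD of adherence 0.170, the MEMS value from the 8-week naltrexone study described in the Background. The protocol does not adopt it as a design assumption, and it serves here only to set a scale.
- R², the share of outcome variance explained by gender and goal together: not given, so varied from 0 to 0.20.

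The calculation treats one adherence value per participant, which is what the between-group main effect of condition rests on.

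**Formulas**
- Reported standard error without the factors: SD × √(2/44) = 0.170 × √(2/44) = 0.0362.
- True standard error under balanced allocation: 0.0362 × √(1 − R²). The overstatement is 1/√(1 − R²) − 1.
- True level of the unadjusted test: 2 × [1 − Φ(1.96/√(1 − R²))].
- Power is taken at the difference with 80% nominal power: (1.960 + 0.842) × 0.0362 = 0.102, or 0.60 SD. Unadjusted power is Φ(0.842/√(1 − R²)); adjusted power is Φ(2.802/√(1 − R²) − 1.96).

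**Results**

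| Assumed R² | True SE | Reported SE too wide by | True level | Power, factors omitted | Power, factors included | Points lost |
|---|---|---|---|---|---|---|
| 0 | 0.0362 | 0% | 0.050 | 80.0% | 80.0% | 0 |
| 0.05 | 0.0353 | 2.6% | 0.044 | 80.6% | 82.0% | 1.4 |
| 0.10 | 0.0344 | 5.4% | 0.039 | 81.3% | 84.0% | 2.7 |
| 0.20 | 0.0324 | 11.8% | 0.028 | 82.7% | 87.9% | 5.2 |

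**Check by simulation** (88 participants, four equally likely strata, blocks of four assumed, 8,000 runs each). The unadjusted test rejected a true null in 0.053, 0.043, 0.037 and 0.029 of runs at R² of 0, 0.05, 0.10 and 0.20. With both factors in the model the rates were 0.052, 0.047, 0.048 and 0.047. The formula and the simulation agree.

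**The case against.** The strongest reply is that the ANOVA follows an 'e.g.'. A General Linear Model can hold blocking factors and covariates, and the list of adjustment variables is commonly left to a statistical analysis plan, which may exist here but is not at hand. That stands. A reader might infer that the protocol commits to a model with condition alone, or that it discards baseline drinking. The documents support neither: the model is illustrative, and the text is silent on baseline drinking.

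A reader might also state flatly that the standard errors will be too wide. That depends on gender or goal predicting the outcome, and the protocol gives no correlation or R² for either. The plausible argument about goal concerns days abstinent, whereas the named ANOVA concerns adherence.

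Two limits on adjustment also stand. Percent of doses taken has no pre-treatment value, since medication starts after baseline, and latency to first heavy drinking day has none either. Covariate adjustment is also not neutral for every outcome: logistic regression for the binary adherence outcome would replace a marginal odds ratio with a conditional one.

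What the reply does not remove is that the one model the protocol puts forward omits the factors it chose to balance on. That can be settled in a sentence before data are seen.

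**Conclusion.** The point holds in conditional form, as a free improvement and not as a validity error. If gender and drinking goal are prognostic, the ANOVA run as named wastes part of what the blocked allocation gains: about 1 to 5 points of power for R² between 0.05 and 0.20, with the standard error 2.6% to 11.8% too wide. If they are not prognostic, nothing is lost. The direction is conservative throughout, so there is no bias in the treatment difference and no inflation of false positives. The figures rest on assumed R² values, equal arms of 44, a two-sided 5% level, and blocking that achieves close balance within strata. No size is claimed for adding baseline drinking, because the protocol gives no baseline-to-outcome correlation.

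**What to change.** In section V, item iii, state the following:

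- Gender and drinking goal enter as fixed factors in the AGATE versus SASED comparison of percent of doses taken and of the continuous drinking outcomes.
- Percent days abstinent, percent heavy drinking days and drinks per drinking day are also adjusted for the baseline value of the same measure.
- The analysis of latency to first heavy drinking day is stratified by gender and drinking goal, with no baseline-value term.
- The binary adherence outcome of Hypothesis 1 is compared by a stratified or standardised risk difference, so that the estimand stays marginal.

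The cost is two degrees of freedom for the two main effects, or three if the four strata are entered separately, plus one for a baseline covariate where used, and slightly more analysis work. Allocation, visits and sample size do not change. If a statistical analysis plan already says this, a cross-reference in item iii is enough.
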